#### Outcomes

The primary outcome of the screening phase is the proportion of people detected with IGR or T2DM using a validated risk tool (positive predictive value). Secondary outcomes include the response rate to the invitation to screening. Those with IGR will be asked if they would like to take part in phase 2 – the diabetes prevention cluster randomised controlled trial.

### Phase 2: Cluster randomised trial

Phase 2 is designed to adhere to internationally recognised criteria for developing complex interventions and for undertaking and reporting cluster randomised controlled trials [33]. Randomisation will be conducted at the level of the GP practice by a researcher who is independent of the study team. Cluster designs are being used in other similar trials of lifestyle management interventions [34-36]. Practices will be randomised 1:1 to either the control arm or the intensive arm using stratification by list size (<6,000, ≥6,000), and ethnicity (% South Asian <21%, ≥21% (median level of % South Asian in the ADDITION-Leicester study [37]) with a block size of 4.

Participation in the study is summarised in Figure 1. A summary of the data collected at each time point is given in Table 1. The primary outcome data will be collected at 36 months. Additional data will be collected at 6, 12 and 24 months. The data collection will follow the same standard operating procedures as the baseline/screening data described in Phase 1. Additionally at the 3 year follow up a health resource one page questionnaire and the EQ-5D will be collected [38]. Records are kept on missed clinical visits; structured education programmes and telephone support as well as withdrawn subjects.

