### Phase 1: the screening phase

#### Identification of those at high risk of having IGR/T2DM

All participating GP practices will receive a Practice Pack giving them general information and contact numbers for the study. All practices will have an induction visit from the project lead and research assistant who will provide training and support.

An automated risk score will be used to identify those at high risk of IGR/T2DM using data routinely stored on individual GP practice computer databases. Various risk scores have been developed and validated for identifying T2DM [23]. Scores available to date have not been validated for the UK multiethnic population and do not additionally pick up those with IGR. Therefore we will use a score developed using data from a previous screening study carried out in Leicester [24]. This score has been amended to take into account ethnicity using the percentage of South Asians within the practice as a proxy for individual ethnicity.

Before the risk tool is applied to a practice database the quality of the data completion is assessed. If the quality level of Body Mass Index (BMI) data recorded is less than 40% practices will be asked to increase this before the risk tool can be used. The score will be calculated for all members of a participating practice. The practice list will then be ranked by risk score with those with the highest scores having the highest risk. The top 10% of patients with the highest score will be invited initially for screening. This 10% limit can be increased to generate further invitations and increase inclusion in the study if required. Where the top 10% of the risk score identifies fewer than 500, all patients within the top 10% will be invited. Where the number of eligible patients identified in the top 10% is greater than 500, the first 500 patients within the top 10% will be invited. If the response rate to initial invitations is insufficient a second mailing of invitations will be conducted. A computer programme will be written to automate the process and produce an excel spreadsheet listing risk scores in descending order.

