#### Intensive arm intervention

Participants in this arm receive the same information booklet as the control arm and in addition are invited to attend an initial six hour structured education programme called Lets Prevent (LP), three monthly nursing support phone calls, and a yearly three hour update structured education programme.

The style, content and process of the programme draws on a range of concepts from health psychology and education [39-42] and its philosophy is centred on patient empowerment [43]. In short, it is a six hour group based education programme that can be either delivered in one full six hour day or in two three hour sessions. The programme has a written curriculum, an outline of which can be seen in Table 2. The key food messages are taken from the Diabetes Prevention Program [44] and the Finnish Prevention Study [45]. Goals are to attain a sustained weight reduction of greater than 5% body weight, moderate reduction in total fat of less than 30% energy intake, low saturated fat intake of less than 10% energy intake and higher fibre intakes of greater than 15 g per 1,000 calories.

**Table 2 T2:** The Lets Prevent curriculum content

Session 1	Theory	Sample Activity	Duration
Introduction	-	-	10 mins
Patient story	CSM	Participants asked to tell their story about how they discovered they had pre diabetes and their current knowledge of pre diabetes	30 mins
Professional story	CSM, DPT	Uses participants’ stories to support them in learning how the body regulates glucose	50 mins
Taking control 1 Weight management	CSM, DPT, SLT	Uses participants’ stories to support them in discovering how weight/waist affects pre diabetes. Provides knowledge and skills for food choices to control weight	30 mins
Physical activity	CSM, DPT, SLT	Uses participants’ stories to support them in discovering how physical activity affects pre diabetes. Provides knowledge and skills for activity choices to manage pre diabetes	40 mins
How am I doing?	SLT	Participants reflect on what issues have come up in the programmes so far	5 mins
Session 2	Theory	Sample Activity	Duration
Reflections	SLT	Participants reflect issues that have arisen in the programme so far	10 mins
Professional story	CSM	Uses participants’ stories to support them in discovering how other risk factors (e.g. blood pressure and cholesterol) affect pre diabetes and the development of complications	30 mins

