### Funding and timescale

The project is funded by an NIHR Programme Grant. Screening started in July 2009 and the last patient should attend their last follow up in July 2014.

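### One fixed, stated block size of 4 in four strata would make about 27–33% of practice allocations certain in advance, if practices are allocated in sequence and recruiters know the block size and past allocations

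*Protocol article*

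**What the plan says.** All of the allocation rule stands in the protocol article, section Phase 2: Cluster randomised trial.

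- Unit and ratio: "Practices will be randomised 1:1 to either the control arm or the intensive arm".
- Strata: "stratification by list size (<6,000, ≥6,000), and ethnicity (% South Asian <21%, ≥21" per cent, which makes 2 × 2 = 4 cells.
- Blocks: "with a block size of 4". No other size, random variation of size, or batching is mentioned.
- Who randomises: the task is done "by a researcher who is independent of the study team".

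The section Power calculation sets the number of practices at 44. Control arm intervention gives that arm a booklet. Intensive arm intervention adds to it: "Participants in this arm receive the same information booklet as the control arm and in addition are invited to attend an initial six hour structured" programme, with regular nurse calls and yearly updates. On practice entry, the screening section says: "All practices will have an induction visit from the project lead and research assistant who will provide training and support". On dates, Funding and timescale says: "Screening started in July 2009 and the last patient should attend their last follow up in July 2014".

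The article does not say whether practices are allocated one by one or together, or whether those who recruit practices know the block size.

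**The concern.** In a 1:1 permuted block of known size, the last allocations follow from the earlier ones. Here the earlier ones can hardly be hidden: one arm runs group sessions and nurse calls, the other hands out a booklet, and a single academic centre coordinates all the practices. Both stratifying factors are practice characteristics that the centre can know. Someone who also knows that every block holds four practices can work out the end of each block without seeing the list.

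The practice is the unit of randomisation and there are only 44. If the person who approaches practices, or decides when one is ready to enter, can foresee the next arm, then the order of entry, or whether a practice is taken on at all, may come to depend on that arm. Differences between practices in motivation would then be confounded with treatment. Practice motivation is not among the listed measures, so adjustment could not reliably remove the confounding.

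The exposure is at practice level only. Block size has no bearing on which patients are selected within a practice that has already been allocated.

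**Working it through.** **Inputs.** Block size 4, ratio 1:1 and four strata come from Phase 2: Cluster randomised trial. The 44 practices, 17 participants per practice, 35% control rate, 40% relative reduction, intra-class correlation 0.05, 20% dropout, 80% power and 5% significance come from Power calculation. The number of practices per stratum is not given, so it is varied below.

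**The plan's own figure.** The article states no predictability figure. Its sample size can be reproduced, which confirms the 44 practices:

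- 35% against 35% × 0.6 = 21%, with the test taken as two-sided: 161 per arm.
- Design effect 1 + (17 − 1) × 0.05 = 1.8, so 161 × 1.8 = 289.8.
- Dropout: 289.8 / 0.8 = 362.2.
- Whole practices: 362.2 / 17 = 21.3, rounded up to 22 per arm. 22 × 17 = 374 per group, and 2 × 22 = 44 practices, as stated.

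**Certain allocations in a block of 4.** An allocation is certain once one arm has used both its places. Over the six possible blocks, positions 1 to 4 are certain with probability 0, 0, 1/3 and 1. Position 3 is certain when the first two match. The sum is 4/3 of every 4 allocations, or 33.3%.

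**Over 44 practices in four strata** (all splits are assumptions):

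- 11/11/11/11: each stratum has two full blocks and three places of a third, so 2 × 4/3 + 1/3 = 3. In total 4 × 3 = 12 of 44 (27.3%).
- 8/8/14/14: 2 × 8/3 + 2 × 4 = 13.3 of 44 (30%).
- 6/8/12/18: 4/3 + 8/3 + 4 + 16/3 = 13.3 of 44 (30%).
- All splits with at least one practice per stratum: minimum 27.3%, maximum 33.3% (44 × 1/3 = 14.7). If each practice is equally likely to fall in any stratum, the mean is 29.5%.

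**Alternatives.** These are simulated for the three splits above, with allocation in sequence and an observer who knows the possible block sizes and all past allocations in the stratum. The best guess is the arm that is behind, or a coin toss at a tie.

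| Block sizes | Certain, of 44 | Best guess correct | Mean absolute arm difference (practices) | 95th percentile |
|---|---|---|---|---|
| 4 fixed | 12.0–13.4 | 68–70% | 1.1–1.5 | 4 |
| 4 and 6 at random | 2.6–2.8 | 67–68% | 1.4–1.6 | 4 |
| 4, 6 and 8 at random | 1.0–1.1 | 65–67% | 1.4–1.8 | 4 |

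Varying the size removes most of the certainty but little of the advantage in guessing. Allocating practices in a batch removes prediction within the batch altogether.

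**The case against.** The strongest reply is that the arithmetic is conditional and the article does not supply the conditions. No sentence says that practices were allocated one at a time. If all 44 were allocated together, nothing could be predicted. The dates do not settle it: they mark the start of screening and the last patient's last visit, and patient screening within practices already on board could run long because of second mailings or a raised invitation limit. Nor does printing the block size in an article that reports screening as already begun show that recruiters knew it at the time. All of this stands, and it is why the point is worded conditionally.

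A reader might infer that about 30% of allocations were in fact foreseeable, or that keener practices were steered to the intensive arm. The documents support neither. The induction visit covers every participating practice and does not show staff choosing or ordering practices by arm. Patients are ranked by an automated score and qualify by glucose test, and list size and percentage South Asian are balanced by the strata. No effect on diabetes incidence can be estimated: the figures measure predictability, not bias.

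Two further replies fail or carry only part of the way.

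- The independent researcher protects the list. That does not prevent deduction from known allocations and a known block size.
- Timing and concealment are details that an article may leave to the full protocol, so their absence alone would be no finding. The single block size, however, is a rule that the article states, and it can be replaced by a better one.

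It is also fair that small blocks serve balance when there are only 44 clusters. The simulation shows that little balance is lost.

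**Conclusion.** The point holds in conditional form. A single stated block size of 4, in four strata of an unmasked cluster trial, makes about 27–33% of practice allocations (12 to 15 of 44) certain in advance if three things are true: practices are allocated in sequence, those who recruit or schedule them know the block size, and they know the earlier allocations in the stratum. The third is plausible because the arms cannot be masked. The first two are not stated either way.

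This is a weakness in the allocation rule, confined to which practices join and when. It is no evidence that selection took place. It merits a change because the change is nearly free, not because the trial's result is shown to be at risk.

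**What to change.** For practices not yet allocated, replace the block-size clause with wording such as: *The independent researcher allocates all practices that have agreed within a stratum together, in batches. Where a practice must be allocated singly, block sizes vary at random (4 and 6) and are not disclosed to the study team until the last practice has been allocated.*

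If allocation is already complete, state instead when practices were allocated relative to recruitment, whether singly or together, and who knew the block size. If they were allocated in one batch, or the size was withheld, one sentence closes the matter.

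Cost: a sentence or two and a new list from the same independent researcher, with no extra practices, visits or patients. With sizes 4 and 6, the expected difference in practice numbers between arms grows by under half a practice, and its 95th percentile stays at 4. The gain should not be oversold: certain allocations fall to about 3 of 44 (6%), but the best-guess success rate falls only from about 68–70% to 67–68%. Batching is therefore the better choice wherever practices sign up in groups.

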**Figure 1 F1:**
[figure not shown]
Study participation.

**Table 1 T1:** Clinical assessment and measures

Measurements	Time points				
	Baseline/Screening	Trial 6 m	Trial 12 m	Trial 24 m	Trial 36 m
	Clinical Assessment					
Medical History	X		X	X	X	
Medication History	X		X	X	X	
Physical Exam	X		X	X	X	
Cardiovascular Risk Score	X	X	X	X	X	
Presence of Metabolic Syndrome	X	X	X	X	X	
	Anthropometric					
3 x Blood Pressure	X	X	X	X	X	
Height	X				X	
Weight	X	X	X	X	X	
Waist Circumference	X	X	X	X	X	
Blood Tests						
Oral Glucose Tolerance Test	X		X	X	X	
HbA1c	X	X	X	X	X	
Lipids	X	X	X	X	X	
Urea & Electrolytes	X		X	X	X	
Liver Function Tests	X		X	X	X	
	Questionnaires & Lifestyle Measures					
IPAQ – SF [31]	X	X	X	X	X	
DINE [27]	X	X	X	X	X	
BIPQ [30]	X	X	X	X	X	
HADS [29]	X	X	X	X	X	
15D [28]	X	X	X	X	X	
	Health care resource use					X
EQ-5D [38]					X	
Sleep questions	X	X	X	X	X	
7 Day Step Count	X	X	X	X	X	
Urine Sample	X		X	X	X	

#### Inclusion criteria

Patients who were eligible for phase 1 are included in the trial if

· Diagnosed with IGR (IGT and/or IFG) at the OGTT at screening/baseline visit

#### Exclusion criteria

Patients are excluded from the trial if they are:

· Diagnosis of diabetes at screening/baseline (if diagnosed during the study participants are invited to continue without the 120 glucose sample or further intervention activities)

#### Control arm intervention

Control subjects receive a booklet detailing information on risk factors for T2DM and how physical activity and lifestyle change can be used to prevent or delay the disease. The leaflet addresses factors around T2DM risk using the five domains (causes, consequences, identity, control/treatment, and timeline) highlighted by Leventhal’s common sense model [39]. The follow up sessions for the control group will occur at the same time points as the intervention group and the same data will be collected.

#### Intensive arm intervention

Participants in this arm receive the same information booklet as the control arm and in addition are invited to attend an initial six hour structured education programme called Lets Prevent (LP), three monthly nursing support phone calls, and a yearly three hour update structured education programme.

The style, content and process of the programme draws on a range of concepts from health psychology and education [39-42] and its philosophy is centred on patient empowerment [43]. In short, it is a six hour group based education programme that can be either delivered in one full six hour day or in two three hour sessions. The programme has a written curriculum, an outline of which can be seen in Table 2. The key food messages are taken from the Diabetes Prevention Program [44] and the Finnish Prevention Study [45]. Goals are to attain a sustained weight reduction of greater than 5% body weight, moderate reduction in total fat of less than 30% energy intake, low saturated fat intake of less than 10% energy intake and higher fibre intakes of greater than 15 g per 1,000 calories.

**Table 2 T2:** The Lets Prevent curriculum content

Session 1	Theory	Sample Activity	Duration
Introduction	-	-	10 mins
Patient story	CSM	Participants asked to tell their story about how they discovered they had pre diabetes and their current knowledge of pre diabetes	30 mins
Professional story	CSM, DPT	Uses participants’ stories to support them in learning how the body regulates glucose	50 mins
Taking control 1 Weight management	CSM, DPT, SLT	Uses participants’ stories to support them in discovering how weight/waist affects pre diabetes. Provides knowledge and skills for food choices to control weight	30 mins
Physical activity	CSM, DPT, SLT	Uses participants’ stories to support them in discovering how physical activity affects pre diabetes. Provides knowledge and skills for activity choices to manage pre diabetes	40 mins
How am I doing?	SLT	Participants reflect on what issues have come up in the programmes so far	5 mins
Session 2	Theory	Sample Activity	Duration
Reflections	SLT	Participants reflect issues that have arisen in the programme so far	10 mins
Professional story	CSM	Uses participants’ stories to support them in discovering how other risk factors (e.g. blood pressure and cholesterol) affect pre diabetes and the development of complications	30 mins
Taking control 2 Food choices: focus on fats	DPT, SLT	Provides knowledge and skills for food choices to reduce risk factors	50 mins
Self management plan	SLT	Participants supported in developing their self management plans	30 mins
Questions	CSM	Checks that all questions raised by participants throughout the programme have been answered and understood	40 mins
What happens next?	SLT	Follow up care outlines	5 mins

CSM: Common sense model, DPT: Dual processing theory, SLT: Social learning theory.

The physical activity messages are taken from the Pre-diabetes Risk Education and Physical activity Recommendation and Encouragement Programme (PREPARE) [12,13]. The PREPARE programme successfully demonstrates that a pragmatic education programme that incorporates pedometer use is effective in improving glucose tolerance in those with IGT. As in the PREPARE programme, participants are provided with a pedometer as a tool for promoting self-regulatory strategies such as goal setting and self-monitoring. The physical activity goal is to achieve an increase in daily walking of 45 minutes or 4,500 steps. Goal attainment is encouraged through the use of proximal objectives such as increasing steps by 500 per day every two weeks.

Following 12 and 24 month clinic appointments, participants are offered the option of attending a three hour update session. The purpose of this update session is to review key messages, review personal risk and action plan. Throughout the three year intervention, participants receive three monthly telephone contacts from nurses trained to support participants with their chosen behaviour change. A quality development programme ensures that the educational intervention is delivered in such a way that the core content and learning outcomes are achieved and the educator behaviours are linked to the programme philosophy and learning theories. The quality development programme consists of internal and external processes adapted from findings from the DESMOND collaborative [46].

Methodologies previously used to effectively modify the DESMOND module to be suitable for those from Black and Minority Ethnic (BME) groups were used to develop the LP BME intervention [47]. The core educational messages are the same as in LP but the programme is culturally appropriate and non reliant on the written word. The LP BME programme is delivered as four sessions of three hours if delivered with an interpreter or two three hour sessions without an interpreter.

#### Endpoints and outcomes

The primary outcome aims to show the reduction in the incidence of T2DM at 36 months in people with screen-detected IGR. Secondary outcomes are reductions in HBA1c, blood glucose levels fasting and post glucose load, cardiovascular risk as calculated by the Framingham risk calculator [48] and the presence of Metabolic Syndrome as defined by NCEP ATP III [49], increasing seven day step count and cost-effectiveness of the intervention.

#### Power calculation

Assuming a 3 year cumulative conversion rate to T2DM of 35% in the control group [44,45,50], an intra class correlation of 0.05 and a dropout rate of 20% (as seen in the Finnish Prevention Study [51]), we calculated that we would need 374 patients to consent per group to detect a 40% risk reduction in the intervention group – data from 44 practices, 17 participants per practice, with 80% power at the 5% significance level. For 17 participants to be recruited per practice we have assumed a participation rate of around 20%. For an average practice 500 people will be invited for screening, of these around 20% will have pre-diabetes (assuming a positive predictive value of 20% [24]). Therefore around 100 participants per practice will be eligible for the trial. Assuming a participation rate of 20% should give the 17 participants we need per practice. A participation rate of 20% has been seen in other studies in a similar population [19].

A 40% reduction in the relative risk of developing T2DM was chosen as a conservative interpretation of the current evidence. Several meta-analyses and a systematic review have shown that lifestyle intervention studies in those with IGT resulted in a ~50% reduction in the relative risk of developing T2DM [5,52,53]. An intention to treat analysis of 12-month follow-up data from a randomised controlled trial found that an intervention aimed at the promotion of physical activity, using methods that are similar to the proposed study, achieved a reduction in 2-hour glucose of 1.3 mmol/l compared to the control group [12]. A reduction of 2-hour glucose of this magnitude has been associated with around a 50% reduction in the relative risk of developing T2DM [52], which is consistent with the above evidence.

One secondary outcome will be the percentage of patients in each group with a 10-year CVD risk greater than 20% at end of 3 years. It is estimated that 55% of patients will have a CV risk greater than 20%. To detect a difference between the two groups of 20% points in the proportion of patients with a 10 year risk of >20% with 80% power and two alpha of 5% and an intra-practice correlation coefficient of 0.05 the required sample size is 180 in the two groups.

